### Intervention and comparison

The OPEN ARCH intervention has two components: fast-track specialist geriatric assessment via a community-based referral to a geriatrician in local GP practices; and an enablement service offering coordination and implementation of health and social care services customised to patient need in the community. The OPEN ARCH intervention will be delivered within primary healthcare. Patients who are deemed eligible by GP screening evaluation and meet inclusion criteria will be invited to provide informed consent. 

During the first interview and assessment, the geriatrician will provide an in-depth, standardised comprehensive geriatric assessment (CGA), a multi-dimensional, interdisciplinary process used to quantify an older individual’s medical, psychosocial and functional capabilities, including diagnosis, identification of problems, goal-setting and forming an individualised comprehensive management plan for holistic treatment, rehabilitation, support and follow up [19]. Alternatively, if the participant is unable to attend the assessment at the practice, a geriatrician will offer a home visit. The type and number of referrals to primary allied healthcare professionals and community support services will be determined by individual clinical needs and delivered in the community (GP, allied health practice or community health centre) or at home. Examples of allied health services that will be offered include: occupational therapy, physiotherapy, dietetics and social work. Community social support services such as personal care assistance, meals and domestic assistance will be arranged through My Aged Care and community health providers.

Upon completion of the initial interview and assessment, the geriatrician and enablement officer will meet with GP via face-to-face case conferencing, to complete the CGA with recommendations. The following Medicare Benefits Schedule (MBS) items will be available to GPs to claim: Item Numbers 735, 739 and 743 [20].

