Based on the CGA recommendations, the enablement officer will meet with participants to develop individual care plans. The enablement officer, who is an advanced health professional specialising in aged care, will further coordinate the participant’s community care by linking them with existing services. Although a registered clinician, their role is not to provide discipline specific services, but rather to draw on existing public, private and non-government allied health, nursing and social support services available in the community to facilitate care coordination goals. All participants will continue to consult with their GPs for usual medical care.

The baseline (pre-intervention or standard care) level of service provision for older patients includes referrals to the Cairns Hospital Outpatient clinic without multidisciplinary care coordination or referral to teams, such as the Aged Care Assessment Team.

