### Economic evaluation

The economic research question is whether the OPEN ARCH intervention is cost-effective in reducing hospital utilisation and enhancing health-related quality of life when compared to the standard care. The perspective for the evaluation model will be a healthcare provider in the Australian setting [27].

Costs of the intervention will be incurred during the CGA and management. The CGA and management costs include the average time with each participant of different personnel, such as a GP, community-embedded specialist in geriatric medicine and community-based care coordinator. Costs of consecutive ED presentations, hospital admissions and hospital length of stay will be included. The cost of the pre-intervention care will include healthcare services utilisation before the initial GP consultation and CGA. Trial initiation, patient accrual and pre-screening activities as well as research and evaluation costs will be recorded and reported separately [28, 29].

Resources will be measured on a patient-specific basis obtained from the purpose-built data input form collated by the project manager from routinely collected computerised patient activity records and medical clinic records, following informed consent processes. Utilisation of objective data is known to eliminate patient recall bias and reduce the amount of missing data [30]. The cost of the time will be derived from a log of time spent on direct patient care activities. A top-down approach will be used to value resource use for capital and operating costs. Healthcare resource use data will be valued using Australian Independent Hospital Pricing Authority standard costs [31] reported in 2018 AUS$.

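### Staff time is costed from a log of direct patient care, so coordination done without the participant present risks being left out of the intervention cost

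*Protocol article*

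**What the plan says.** **How staff time is costed.** Under Economic evaluation, the protocol article says of the intervention cost: "The CGA and management costs include the average time with each participant of different personnel". The personnel given as examples are a GP, the geriatrician and the care coordinator. The source of the time is then given: "The cost of the time will be derived from a log of time spent on direct patient care activities". Two neighbouring sentences also matter: "Resources will be measured on a patient-specific basis obtained from the purpose-built data input form", and "A top-down approach will be used to value resource use for capital and operating costs". Trial initiation, accrual, pre-screening, research and evaluation costs are to be recorded and reported separately.

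**What the staff do.** The section headed Intervention and comparison opens its account of the model thus: "The OPEN ARCH intervention has two components: fast-track specialist geriatric assessment via a community-based referral to a geriatrician in local GP practices". The second component is described as "an enablement service offering coordination and implementation of health and social care services customised to patient need in the community". The enablement officers are registered clinicians, but "their role is not to provide discipline specific services, but rather to draw on existing public, private and non-government allied health" and other services. After the first assessment, "the geriatrician and enablement officer will meet with GP via face-to-face case conferencing, to complete the CGA with recommendations". The enablement officer also meets participants to develop care plans. Standard care is described as lacking multidisciplinary care coordination.

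**What the cost is meant to cover.** The abstract says that costs include implementing the intervention and the later use of services. The perspective is that of a healthcare provider. The ICER is built on mean cost and mean QALYs in the intervention and pre-intervention periods, with a willingness to pay of AUS$64,000 per QALY.

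**The concern.** The costing rule is worded for contact time: time with the participant, taken from a log of direct care. The second component is largely a different kind of work: finding services, referring, liaising and following up. To a healthcare provider that time costs the same whether or not the participant is in the room. If the log is kept as the sentence reads, part of the cost of running OPEN ARCH may never be recorded.

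The error would have a direction. Standard care has no matching coordination, so a gap would lower intervention-period cost and leave pre-intervention cost untouched. The ICER would then look better than it should. The article reports that the trial was 6 months post baseline in November 2018, and activity that was not logged is hard to reconstruct later.

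**Working it through.** The plan states no intervention cost, staff hours, wage rate or split between contact and other time, so there is no figure to reproduce. The check has a textual part and a range calculation.

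**1. Is the time clearly inside the costing rule?**

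| Activity in Intervention and comparison | Captured by a direct-care log? |
|---|---|
| Geriatrician's assessment, at the practice or at home | Yes, contact time |
| Enablement officer's care-plan meeting with the participant | Yes, contact time |
| Case conference of geriatrician, enablement officer and GP | Not clearly. It completes the CGA, which is a costed item, but no participant is mentioned |
| Linking to services and coordinating them | Not clearly. Much of it can be done without the participant |

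The log covers the cost of time. The top-down method is assigned, in a separate sentence, to capital and operating costs. Whether staff salaries count as operating costs is not stated. If they do not, unlogged time is lost. If they do, logged time may be counted twice.

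**2. How much staff cost could be missed?** Let *h* be the share of staff cost that is coordination, and *f* the fraction of that which is away from the participant and unlogged. Both are assumed.

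Understatement of staff cost = *h* × *f*

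| *h* | *f* = 0.25 | *f* = 0.50 | *f* = 0.75 | *f* = 1 |
|---|---|---|---|---|
| 0.3 | 7.5% | 15% | 22.5% | 30% |
| 0.5 | 12.5% | 25% | 37.5% | 50% |
| 0.7 | 17.5% | 35% | 52.5% | 70% |

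If the log or the top-down costing already picks up this time, *f* = 0 and the understatement is 0%.

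**3. What is an omitted amount worth?** Input: AUS$64,000 per QALY (Economic evaluation). An omitted cost *c* per participant raises net monetary benefit by *c*, which equals *c* / 64,000 QALY:

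- AUS$500: 500 / 64,000 = 0.0078
- AUS$1,000: 1,000 / 64,000 = 0.0156
- AUS$2,000: 2,000 / 64,000 = 0.0313

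The dollar amounts are illustrations.

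**4. Does the average matter?** It does not matter for the mean cost in the ICER, because replacing individual values by their mean leaves the mean unchanged. It would matter for the standard error if one common value were assigned to everyone. Let *r* be SD(staff cost) / SD(other cost) and ρ their correlation, both assumed.

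SE ratio (common average / individual times) = 1 / √(1 + *r*² + 2ρ*r*)

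- *r* = 0.1, ρ = 0: 1 / √1.01 = 0.995
- *r* = 0.25, ρ = 0.3: 1 / √1.2125 = 0.91
- *r* = 0.5, ρ = 0.5: 1 / √1.75 = 0.76

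The effect on uncertainty would run from negligible to moderate.

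**The case against.** The best defence is that direct patient care is undefined and may mean work attributable to a patient as opposed to research work. The section does separate research and evaluation costs, and on that reading nothing is missing. The case conference completes the CGA, which is a costed item, and the list of costs is introduced by a verb that does not make it exhaustive. Top-down operating costs might absorb the rest. The sensitivity analysis covers specific cost impacts. Log categories are also detail that a condensed article can leave to a fuller document.

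Much of this stands as a reason not to claim a certain bias. It does not settle the matter. Research costs are already set aside in their own sentence, so the word direct is not needed for that purpose, and the phrase about time with each participant points to contact. The top-down sentence does not say that it covers staff. Staff time is not named in the sensitivity analysis. The point concerns the rule that the article does state, not missing detail.

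A reader might infer two stronger things, and the documents support neither:

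- *That half of the intervention happens away from the patient.* Coordination is one of two named components, but no share of time or cost is given. Care-plan meetings and geriatrician home visits are contact time, and staff travel is not mentioned at all.
- *That variation between patients is lost.* The same section says that resources are measured per patient, and nowhere says that a common mean is assigned to everyone. Measuring individually and summarising by an average is not a contradiction.

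**Conclusion.** The concern holds as a risk created by the wording. A costing rule framed around contact time is poorly matched to an intervention with coordination as one of its two components. Followed literally, it could leave real provider cost out of the intervention side only and move the ICER towards cost-effectiveness.

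The documents do not show that cost is in fact understated, or by how much. The worked range of 0% to 70% of staff cost rests wholly on assumed shares, and the zero end is a legitimate reading of the text. Only the conversion rate comes from the plan: about 0.016 QALY per AUS$1,000 omitted. On averaging, all that remains is that individual times should be carried into the uncertainty analysis. The point is worth correcting because the possible error has a known direction and the correction is cheap.

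**What to change.** Replace the two sentences on staff time under Economic evaluation with wording such as:

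*Geriatrician, enablement-officer and GP time will be logged and costed for each participant for all intervention activities attributable to that participant: assessment, care planning, case conferences, liaison and referral, and any travel. Research and data-collection time is excluded. Top-down costing of capital and operating costs excludes this staff time. Participant-level times will be used in the analysis of uncertainty.*

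If only contact time has been logged so far, use the salary cost of these staff, net of research time and allocated over the participants served, as the base case, with contact-only time as a sensitivity analysis. The deduction is needed because the outcome sections give record keeping and a share of secondary-outcome data collection to engagement officers, who appear to be the enablement officers. Allocating full salaries would load research work onto the intervention.

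The cost is a few more categories on a log already planned, or an allocation from salaries. The downside is slightly more logging and a higher, less favourable intervention cost.

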#### Frequency of analyses

All data will be collected at baseline ‘0’ with retrospective collection for 3 months to time point ‘– 1’, following every 3 months of data collection, at time points ‘1’, ‘2’ and ‘3’ (see Fig. 2), except for participants’ experiences, which will be collected at the end of the study period.

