**Methods/design:**

This multicentre randomised controlled trial uses a stepped wedge cluster design with repeated cross-sectional samples. General practitioners (GPs; *n* ≥ 10) will be randomised as ‘clusters’ at baseline using simple randomisation. Each GP cluster will recruit 10–12 participants. Data will be collected on each participant at 3-month intervals (− 3, 0, 3, 6 and 9 months). The primary outcome is health and social service utilisation as measured by Emergency Department presentations, hospital admissions, in-patient bed days, allied health and community support services. Secondary outcomes include functional status, quality of life and participants’ satisfaction. Cost-effectiveness of the intervention will be assessed as the change to cost outcomes, including the cost of implementing the intervention and subsequent use of services, and the change to health benefits represented by quality adjusted life years.

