#### Secondary outcomes measures

Secondary outcomes will comprise: functional status as measured by the Functional Independence Measure [22] and Seniors at Risk (ISAR) screening tool [23]; quality of life (QoL) as measured by EQ-5D-5L [24] and AQOL-8D [25]; and patient experience of the OPEN ARCH intervention collected via the PSQ-18 questionnaire [26]. The secondary outcomes data collection will be shared between the project manager and engagement officers.

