### Statistical methods to assess intervention effect

The primary outcome measures, including Emergency Department (ED) presentations, hospital admissions, in-patient bed days, allied health and support services utilisation, will be analysed as panels between each cross-sectional time point of the stepped wedge design, comparing primary outcomes within and between clusters. Each cross-section will include participants undertaking the intervention as well as those receiving standard care (pre-intervention component). In addition to assessing intervention effects, the stepped wedge design can also model the effects of time to determine whether the time of intervention (intervening early versus intervening late) impacts the effectiveness of the intervention. Secondary outcome measures, including functional status, ISAR and QoL measures, will be compared for the pre versus post intervention periods, for each participant, and thus the participants will act as their own control. Participants’ experience of the OPEN ARCH intervention as measured by the Likert scale responses will be analysed using descriptive statistics.

Within-cluster and between-cluster variance, treatment outcomes for intervention versus pre-intervention, across time, will be examined by applying a generalised linear mixed model (GLMM), as recommended for small cluster designed stepped wedge studies [16]. GLMM models can be adjusted for unequal numbers within clusters and cope with non-parametric data distributions. Within the GLMM, primary and secondary outcomes will be assessed against time and intervention status, represented as fixed effects, while study clusters and clients will be represented in the model as random effects [16]. Secondary outcome analyses will include *t* tests (for continuous data), chi-square tests (for proportions) and GLMMs where applicable, to control for demographic differences. All statistical tests will be two-sided and performed using a 5% significance level with no adjustment for multiplicity. Data analysis will be performed using STATA version 15 [18].

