### Limitations

The study populations are, by definition, at risk of natural functional and cognitive decline that may be marked over the study period. Although the study design applies multiple methods to best capture intervention effects, the benefits in slowing down deterioration may not be successful in some participants due to their frailty. Within the quantitative methods are cross-sectional and case–control (pre–post intervention) analysis, which will assess between and within clusters differences. The pre–post analyses will utilise paired analyses where each participant acts as their own control. These methods plus the inclusion of qualitative surveys should tease out even minor benefits of OPEN ARCH, when presented with accelerated decline. The sample size calculation has allowed attrition, so these factors should allow statistical significant effect size within OPEN ARCH achievable.

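### Read literally, the retrospective month −3 collection covers FIM, ISAR, EQ-5D-5L and AQOL-8D, so reconstructed scores could enter only the pre side of the paired comparison

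*Protocol article*

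**What the plan says.** All references are to the protocol article.

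- **Frequency of analyses:** "All data will be collected at baseline ‘0’ with retrospective collection for 3 months to time point ‘– 1". Collection then continues every 3 months at points 1, 2 and 3. The one exception is participants' experiences, "which will be collected at the end of the study period".
- **Abstract, Methods/design:** "Data will be collected on each participant at 3-month intervals (− 3, 0, 3, 6 and 9 months". Month −3 is listed like the other four points, with no restriction by outcome.
- **Secondary outcomes measures:** "functional status as measured by the Functional Independence Measure [22] and Seniors at Risk (ISAR) screening tool [23", plus EQ-5D-5L and AQOL-8D for quality of life. The project manager and the officers collect these; no record source for a past score is given.
- **Primary outcome measures and Economic evaluation:** hospital and ED use come from routine computerised records, and other service use from clinic records. Protection against recall bias is claimed for these resource data.
- **Statistical methods to assess intervention effect:** "Secondary outcome measures, including functional status, ISAR and QoL measures, will be compared for the pre versus post intervention periods, for each participant". The same section also puts secondary outcomes in a GLMM with time and intervention as fixed effects, where applicable; the coding of time is not given.
- **Limitations:** "The pre–post analyses will utilise paired analyses where each participant acts as their own control".

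**The concern.** Looking back 3 months is sound for events held in a record. It is not sound for a score that describes a person's state on a given day, unless someone scored it on that day. The article names no such source for the four instruments, so a month −3 value would have to be rebuilt at the baseline contact. The eligible population includes people with early-onset dementia, and Limitations describes the participants as at risk of cognitive decline.

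From month 0 onward the instruments are scored at the time. Every reconstructed value would therefore be a standard-care value and none an intervention value. A change in how the outcome is measured would partly coincide with the contrast of interest. This is separate from the natural decline that Limitations acknowledges, because it would arise even if function were perfectly stable.

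At stake are the research questions on functional decline and on quality of life. EQ-5D-5L and AQOL-8D also generate the QALYs, and the ICER contrasts intervention with pre-intervention periods.

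**Working it through.** The plan gives no figure to reproduce. The check asks how much of an error at month −3 would reach the estimate.

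**Inputs from the article.** Five time points, −1, 0, 1, 2 and 3 (months −3, 0, 3, 6 and 9), of which only −1 is retrospective; a staggered start; a within-person pre-versus-post comparison.

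**Assumptions.** (a) Three steps, crossing over after points 0, 1 and 2. (b) The paired analysis averages all pre values and all post values. (c) A common systematic error of d units at point −1 only, no true effect and no trend.

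**Paired contrast.** With n_pre pre-intervention points, the pre mean shifts by d / n_pre and the post mean by 0, so the bias of post minus pre is −d / n_pre.

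| Crossover after | n_pre | n_post | Retrospective share of pre values | Bias |
|---|---|---|---|---|
| month 0 | 2 | 3 | 1/2 | −0.50d |
| month 3 | 3 | 2 | 1/3 | −0.33d |
| month 6 | 4 | 1 | 1/4 | −0.25d |

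The retrospective share of post values is 0 in every row.

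**Pooled within-step fit without time.** Each step is weighted by n_pre × n_post, that is 6, 6 and 4:

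−(6 × 1/2 + 6 × 1/3 + 4 × 1/4)d / 16 = −6d / 16 = −0.375d.

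**Adding time.** Least-squares fits on the same layout, with step intercepts:

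- Linear time: +0.375d. With a random intercept in place of step intercepts (correlation 0.1 or 0.5) the figure is +0.30d to +0.35d. It also depends on the number of steps.
- Categorical time: 0. Everyone is untreated at point −1, so the effect of that period takes up a common shift. A shift that differed between steps would not be fully absorbed.

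**Sensitivity to the assumptions.** If everyone's last pre-intervention point is month 0, the share is 1/2 throughout. If the paired test uses only the last pre-intervention value, the share is 0.

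**Cost of dropping point −1.** Generalised least squares with categorical time, 10 GPs split 3/3/4, cluster ICC 0.10 and 9 evaluable participants per GP (120 × 0.75 / 10). The ratio of standard errors without and with point −1 is 1.042, 1.050 and 1.057 for assumed within-person correlations of 0.2, 0.5 and 0.8.

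**The case against.** The strongest reply is that the sentence was never meant for questionnaires. It describes collection over a 3-month interval, which suits event counts, and the authors show in the Economic evaluation that they value objective records because they avoid recall bias. On that reading the instruments start at month 0 and only utilisation looks back. Figs. 1 and 2 and the SPIRIT file, none of them shown, may say so. This stands as far as intent goes: nowhere does the article say that FIM or any other score is recalled, and a reader who infers that it is goes beyond the text. It does not rescue the wording, which says all data and names one exception that does not cover these instruments.

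Three further points stand:

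- Averaging of pre values is not stated. A test on the last pre-intervention value would not touch month −3.
- The assumed layout gives clusters about 9, 6 and 3 months of intervention by month 9, while Randomisation of general practitioners promises all clusters equal duration. The fractions are therefore illustrative.
- A reader might infer that the two planned analyses will disagree in sign. That needs linear time, which the article does not specify; the coding of time may properly be left to a statistical analysis plan.

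**Conclusion.** The point holds in a limited form. As written, the article includes FIM, ISAR, EQ-5D-5L and AQOL-8D in a retrospective month −3 collection that only service use can support. Any such score would sit solely on the pre side of a paired comparison.

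Under assumptions (a) to (c), one half, one third or one quarter of a systematic error would enter the contrast by step. Under other readings of the paired test the fraction runs from 0 to one half. The GLMM is protected against a common shift if time is categorical and is not protected if time is linear.

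It would be tempting to say that the functional-status comparison is biased, or to attach a number of FIM points to it. The documents do not support either statement: they give no size or direction for the error, and they do not confirm that these scores are collected for month −3. The outcomes affected are secondary, together with the QALYs built on them. The wording needs correction on either reading of the sentence.

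**What to change.** In the abstract's Methods/design and in Frequency of analyses, limit the retrospective month −3 point to record-based service use: ED presentations, admissions, bed days, and allied health and support services where clinic records exist. State that FIM, ISAR, EQ-5D-5L and AQOL-8D start at month 0.

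Trial status puts the study 6 months past baseline in November 2018, so month −3 scores may already exist. If they do, leave them out of the pre-post comparisons and enter time as categorical in the secondary-outcome GLMM. The bias from this source in the paired contrast is then 0, and under the assumed layout each participant keeps 1, 2 or 3 pre-intervention values scored at the time.

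The cost is a change of wording and an analysis exclusion, with no extra participants or data and no loss of baseline for the primary outcomes. Precision falls slightly: the standard error of the intervention effect rises by about 4% to 6% under the assumptions above.
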